#### 2.4.2. Exclusion Criteria

The exclusion criteria for HS are the same as the criteria for FC patients (see Section 2.3.2). Moreover, those who have possible organic diseases, psychological disorders, and gastrointestinal symptoms and signs are also excluded.

### 2.5. Recruitment Strategy

The participants will be recruited from the Chengdu University of Traditional Chinese Medicine (CDUTCM) by delivering leaflets inside the campus, posting advertisements in billboards, posting at Acupuncture and Brain Science Research Center and CDUTCM (http://cdutcm.edu.cn/) websites, and posting in our WeChat public account.

### 2.6. Intervention

The participants will undergo 40 sessions with 24-style Tai Chi. The exercise of Tai Chi will be performed four times a week (Monday, Tuesday, Thursday, and Friday) and will last for 10 weeks [15]. Each exercise session lasts for an hour, including 10-minute warm-up, 40-minute Tai Chi exercise, and 10-minute relaxation.

Before the formal intervention, participants were involved in motor learning and strength training under the guidance of two professional Tai Chi instructors. During the intervention, they exercise strictly under the 24-style Tai Chi exercise standard operating procedure (SOP), which was formulated by two Tai Chi experts. In each session of the exercise, the instant heart rate will be counted both at the pre- and posttrial, and the sports self-rating scale will also be filled out. Participants who did not come will be recorded. The training will be considered effective when the rating of perceived exertion (RPE) of the subjects reaches 4–6 levels in each session, and training times must not be less than 80% (32 times) of total training times.

During the treatment period, participants are usually not recommended to use concomitant care or interventions. However, if required (such as, aggravation of the patient's condition), participants will be permitted to use extra osmotic laxatives. The type and dosage of medication used should be recorded in the case report forms (CRFs).

### 2.7. Outcome Measurements

Measurements will be evaluated by independent assessors who have been trained prior to the study. All results will be recorded whether or not the participants completed the study. The outcome assessors will be independent of the research team and will not be told about group allocation, so as to ensure the object evaluations of the trial.

#### 2.7.1. General Information Collection

Same as our previous study [15], general information including the demographic data and vital signs will be collected. The demographic data include age, gender, education level, nationality, and body mass index (BMI). The vital signs include body temperature, heart rate, respiratory rate, and blood pressure. Among them, the BMI will be calculated at the baseline and the end of the invention, whereas the vital signs of each patient will be immediately recorded after every training.

According to our hypothesis, the nonspecific effects of Tai Chi include motor function, vital capacity, and psychological state regulation and the specific effects of Tai Chi for FC patients reflects in relieving gastrointestinal symptoms and modulating autonomic nerve function.

#### 2.7.2. Nonspecific Effects: Motor Function, Vital Capacity, and Psychological State

The lower-extremity muscle strength, functional balance tests, and the vital capacity test will be collected at the baseline, the median of intervention (after 5 weeks of exercise), and at the end of the intervention. The lower-extremity muscle strength will be measured using a hand-held isometric dynamometer (Micro FET3; Hoggan Health Industries, Draper, UT, United States). Functional balance tests include the Berg Balance Scale (BBS) [16], timed up-and-go (TUG) test, and functional reach test [17].

During the vital capacity test, the forced expiratory volume in one second (FEV1), forced vital capacity (FVC), and FEV1/FVC ratio will be measured using a Super Spiro spirometer (MicroMedical, Rochester, Kent, UK) in resting status. The peak expiratory flow rate (PEFR) will be assayed using a peak flow meter.

To assess the psychological state of all participants, we collected the following metrics at the baseline, the median of intervention, and the end of intervention: the self-rating depression scale (SDS) [18], the self-rating anxiety scale (SAS) [19], and the Eysenck Personality Questionnaire (EPQ) [20].

#### 2.7.3. Specific Effects: Gastrointestinal Symptoms and Autonomic Nerve Function

To evaluate the changes of the gastrointestinal symptoms and QOL of participants, we performed the following measurements at the baseline, the median of intervention, and the end of intervention: CCS [21], patient assessment of constipation symptoms (PAC-SYM) [22], patient assessment of constipation QOL questionnaire (PAC-QOL) [23], RPE [24], and MOS 36-item short-form health survey (SF-36) [25]. Also, the evaluation of constipation diary, including CSBMs per week, the fecal character, and the difficulty degree of defecation, will be measured once a week for 10 times.

To evaluate the autonomic nervous function, we selected the heart rate variability (HRV). All participants will be assessed during the 24-h HRV at the baseline and the end of the intervention. The metrics of HRV include standard deviation of NN intervals (SDNN), standard deviation of sequential 5-min RR interval means (SDANN), and root mean square successive difference (RMSSD). The device used is a dynamic electrocardiogram (ct-086S; BENE WARE, Hangzhou, China).

### 2.8. MRI Data Acquisition

MRI data will be collected on 15 participants in each group at the baseline and the end of intervention. The acquisition parameter will be consistent with our previous article [15].

The MRI scan includes three sequences: a high-resolution 3-dimensional T1-weighted imaging (3D-T1W1), a blood oxygenation level-dependent functional MRI (BOLD-fMRI), and a diffusion tensor imaging (DTI) sequence. Scanning will start in the morning after overnight fasting. Subjects who are selected will undergo MRI scan with a 3.0 T magnetic resonance scanner (Siemens, Germany). The 3D-T1WI scan parameters will be as follows: repetition time/echo time: 1900 ms/2.26 ms; slice thickness: 1 mm, slice number: 176, matrix size: 128 × 128, and the view field: 256 × 256 mm^2^. The BOLD-fMRI scanning parameters are as follows: repetition time/echo time: 2000 ms/30 ms; flip angle: 90°; slice number: 30; matrix size: 128 × 128; view field: 240 × 240 mm^2^; slice thickness: 5 mm; and total volume: 240. DTI data are as follows: view field: 240 × 240 mm^2^; repetition time/echo time: 6800 ms/93 ms; matrix size: 128 × 128; and slice thickness: 3 mm, seamless. Two diffusion-weighted sequences will be acquired using gradient values b: 1000 s/mm^2^ and b: 0, with diffusion-sensitizing gradients used in 64 noncollinear directions.

### 2.9. Data Management

The clinical data will be managed with printed and electronic CRFs. CRFs will be entered parallelly and will only be available to the outcome assessors. The Evidence-based Medicine Center of the CDUTCM will be responsible for monitoring the study and data every 3 months.

### 2.10. Statistical Analysis

#### 2.10.1. Clinical Data Analysis

Clinical data will be analyzed by independent statisticians who do not know the test procedure based on the principles of intention to treat (ITT) and per protocol. The statistical significance threshold has *p* value <0.05. The results of the participants who failed to complete the study will be considered no different from the baseline data in ITT analysis. All continuous variables will be presented as mean ± standard deviation. The categorical variables will be described in percentage (%). The clinical data in the two groups (FC group and HS group) will be compared with two-sample *t*-tests, and the comparisons of the baseline and after intervention in each group will be compared with a paired sample *t*-test. Nonparametric tests (Mann–Whitney *U* test) will be used to compare nonnormally distributed clinical data, and the *χ*^2^ test or Fisher's test will be used to compare categorical variables.

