#### 2.10.2. Functional MRI Data Analysis

For fMRI scans, all preprocessing steps will be performed using DPABI software based on MATLAB. The main analytical methods include the amplitude of low-frequency fluctuation amplitude (ALFF) and seed-based functional connectivity.

After preprocessing the data, the ALFF will be calculated to compare the whole-brain spontaneous activity pattern before and after intervention in each group, as well as between patients with FC and HS following 10-week Tai Chi practices. The different regions obtained at ALFF analysis will be selected as the region of interest (ROI), also called seed, to perform the seed-based functional connectivity analysis and to explore the functional synchronization of ROI and other regions. The thresholds of *p* < 0.05 with a false discovery rate correlation will be applied to all analyses.

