#### 2.10.3. Correlation Analysis

To investigate the associations between nonspecific effects and central responses under different physical conditions, we performed the correlation analysis between the clinical data, including motor function, respiratory function, psychological state, and cerebral function in patients with FC and HS. In order to further explain the regulation mechanism of Tai Chi on the brain-gut interaction disorder, the correlation analysis among gastrointestinal symptoms, heart rate variability, and brain function activities in FC patients will also be carried out.

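### One unadjusted p<0.05 covers about 66 clinical tests with no outcome ranked first, and the clinical–brain correlations in 15 people per group have no stated threshold

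*Protocol article*

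**What the plan says.** Section 2.10.1 (Clinical Data Analysis) gives the clinical data one threshold: "The statistical significance threshold has" a p value below 0.05. For FC against HS, the variables "will be compared with two-sample" tests. Change over time is tested separately, once in FC patients and once in HS: "the comparisons of the baseline and after intervention in each group will be compared with a paired sample" test. Nonparametric or categorical tests are used where needed. Analyses are "based on the principles of intention to treat (ITT) and per protocol". The section names no primary outcome, ordering or adjustment.

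Sections 2.7.2 and 2.7.3 list the outcomes. The only outcome with a sample-size basis is the weekly number of complete spontaneous bowel movements (CSBMs) in FC patients (Section 2.2, one-sample noninferiority test). Section 2.10.1 does not mention that test.

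Multiplicity is addressed once, at the end of Section 2.10.2 (Functional MRI Data Analysis): a threshold of p<0.05 "with a false discovery rate correlation will be applied to all analyses".

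Section 2.10.3 then relates motor, respiratory and psychological measures to cerebral function in both groups, and adds "the correlation analysis among gastrointestinal symptoms, heart rate variability, and brain function activities in FC patients". It states no number of pairs, threshold or correction. Section 2.8 limits MRI to 15 participants per group.

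**The concern.** The trial's aim is answered by a pattern over many outcomes. The Discussion says the existence of specific and nonspecific effects will be explored by comparing motor, respiratory, gastrointestinal, psychological and heart-rate-variability (HRV) results between FC patients and HS. With dozens of tests at the same unadjusted level and none ranked first, chance positives can enter that pattern and be labelled specific or nonspecific.

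The correlations carry a further risk. Those in FC patients are meant to help explain a brain–gut mechanism. With 15 people per group, a correlation must be large to reach significance, so those that do will tend to overstate the true association.

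**Working it through.** **1. The plan's own figure.** The article gives no test count or familywise error rate. Its one relevant figure is the CSBM sample size of 36. Formula (1) with σ = 0.89, μ − μ₀ = 1.67 − 1.8 = −0.13, α = 0.05 and power 0.80 needs a noninferiority margin that the article does not print. Assuming a margin of 0.5 and a one-sided test: (0.89 × (1.645 + 0.842) / (0.5 − 0.13))² = 35.8, so 36, and 36/0.90 = 40. Margins of 0.4 and 0.6 give 68 and 23. So 36 is consistent with one CSBM test at the full 0.05, if the margin was 0.5.

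**2. Count of clinical tests (my count, Sections 2.7.2 and 2.7.3).**

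| Domain | Variables | Number |
|---|---|---|
| Motor | muscle strength, BBS, TUG, functional reach | 4 |
| Respiratory | FEV1, FVC, FEV1/FVC, PEFR | 4 |
| Psychological | SDS, SAS, EPQ | 3 |
| Scales | CCS, PAC-SYM, PAC-QOL, RPE, SF-36 | 5 |
| Diary | CSBMs, stool character, difficulty | 3 |
| HRV | SDNN, SDANN, RMSSD | 3 |
| **Total** | | **22** |

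Three tests each (FC vs HS, before–after in FC, before–after in HS): 22 × 3 = 66. Subscales, the week-5 visit and the second analysis set are left out; testing both ITT and per protocol would give 132.

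**3. False positives among the 66.**
- Expected number if all nulls are true: 66 × 0.05 = 3.3, whatever the correlation.
- Not all nulls are plausible. FC patients must have CCS above 10 and fewer than three CSBMs a week (Section 2.3.1), while HS with gastrointestinal symptoms are excluded (Section 2.4.2). Setting aside the six FC-vs-HS tests on CCS, PAC-SYM, PAC-QOL and the diary items leaves 60 × 0.05 = 3.0. If the hoped-for motor and respiratory gains in both groups are also real (8 × 2 = 16 paired tests), 44 × 0.05 = 2.2 remain.
- Chance of at least one, all nulls true: 1 − 0.95⁶⁶ = 0.966 if all tests were independent. They are not, since the between-group comparison reuses the data of the two paired tests. A simulation with that sharing (between-group test taken on change) gives 93%, 86%, 74% and 56% for correlations between outcomes of 0, 0.3, 0.5 and 0.7.

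**4. Clinical–brain correlations (Section 2.10.3).** The number of brain regions is not known in advance; I assume 3–5.
- HS: motor 4 + respiratory 4 + psychological 3 = 11 measures, so 33–55 pairs.
- FC: those 11 + gastrointestinal 6 (CCS, PAC-SYM, PAC-QOL and three diary items) + HRV 3 = 20 measures, so 60–100 pairs.
- At an assumed 0.05 with all nulls true: 33–55 × 0.05 = 1.7–2.8 in HS, and 60–100 × 0.05 = 3–5 in FC.

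**5. What n = 15 can show.** With 13 degrees of freedom t = 2.160, so the critical |r| = 2.160/√(13 + 2.160²) = 0.514. By simulation at a true r of 0.3, power is 19% and the mean of the significant estimates is about 0.61, twice the truth. For a true r of 0.5, power is about 47% (Fisher z approximation). Symptom–HRV pairs in FC patients need no scan and can use up to 40 patients, so these figures do not apply to them.

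**The case against.** The strongest objection is that this is a condensed article. An analysis plan may exist, and multiplicity families and correlation thresholds are often left to it. That stands in part: a reader might infer that the trial has no multiplicity control, but the article shows only that none is stated here for the clinical tests. It does not dispose of the point, because the article does more than stay silent. It fixes a clinical threshold without correction and an imaging threshold with one.

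A reader might also infer that the correlations will be judged at an uncorrected 0.05. Section 2.10.3 gives no threshold. The FDR sentence refers to all analyses; its place limits it to imaging, but its wording does not strictly exclude correlations with brain measures.

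Two larger figures are tempting. A 97% familywise error requires full independence, and 3.3 false positives requires every null to be true. Nor does each group have all 22 measures correlated with the brain: HS has 11 and FC has 20.

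Finally, no passage says that effects will be declared by counting significant tests, and the article already calls the central responses potential and the work exploratory. That is fair, and it softens the point. But the stated purpose is still to establish whether the effects exist, and the FC correlations are still introduced as explaining a mechanism.

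**Conclusion.** The point holds as a weakness that should be corrected, not as a flaw that invalidates the trial. Section 2.10.1 as written applies an unadjusted 0.05 to about 66 clinical tests with no outcome priority. The expected number of false positives is at most 3.3 on that count, and the chance of at least one under the global null is roughly 56–93%. These figures rest on my count of tests and on outcome correlations of 0 to 0.7.

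For the correlations, the supportable statement is that threshold, correction and family are not given. The 2–3 (HS) and 3–5 (FC) false positives depend on an assumed 0.05, 3–5 regions and all nulls true. The n = 15 limits apply only to pairs that include a brain measure; correlations found there cannot carry a mechanistic claim.

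**What to change.** 1. In Section 2.10.1, name the CSBM change in FC patients as the single primary test at 0.05, using the one-sample noninferiority test on which the trial is sized (not the paired test against zero), and state its margin.
2. Apply the FDR already chosen for imaging within each clinical domain (motor, respiratory, psychological, gastrointestinal, HRV), assigning SF-36 and RPE to a domain, or label these tests exploratory.
3. In Section 2.10.3, define the correlation family and apply FDR across it, or label it exploratory. Report each correlation with its n and 95% confidence interval, as hypothesis-generating and not as explaining mechanism. Reword the FDR sentence in Section 2.10.2 to say which analyses it covers.

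The cost is a few lines of text and code and some power on secondary outcomes: in a five-measure domain, the smallest p value is judged first at 0.05/5 = 0.01. The sample size stays at 36 (40 recruited). Bonferroni over all 66 tests (0.05/66 = 0.00076) would be far dearer: with the assumed margin of 0.5, the CSBM test would need 94 patients, and power at 36 would fall from 80% to 25%.

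This controls chance findings only. A test within FC patients cannot by itself separate specific from nonspecific effects, and FDR does not make a contrast between significant and non-significant results valid evidence of a difference.

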On the basis of the characteristics of Tai Chi and previous researches, we predict that the effects of Tai Chi include two aspects: the relatively specific effects and nonspecific effects. The nonspecific effects mainly refer to the modulating effects on human motor function (muscle strength, physical flexibility, etc.) and respiratory function, especially vital capacity. The nonspecific effects might also manifest as maintaining the normal function of organs/systems, keeping the body in a relatively balanced and coordinated state. While the relatively specific effects of Tai Chi are disease-oriented, meaning that when the body is in a pathological state, Tai Chi practice might reduce the hyperactive function to improve the hypoactive function.

To test the hypothesis, we design this neuroimaging study. In this study, both functional constipation (FC) patients and HS were selected as participants to investigate the specific effects (gastrointestinal function) and nonspecific effects (motor function and respiratory function) of Tai Chi. FC is a common functional gastrointestinal disorder (FGID) with high prevalence. It is characterized by various constipation-related symptoms, including reduced defecation, defecation stress, hard stools, and uncomfortable abdominal muscle in the absence of evident organic or structural reasons for these symptoms. A randomized control trial indicated that Tai Chi practice could significantly improve the constipation symptom of patients with chronic FC [11].

This study aims to (1) investigate the nonspecific effects of Tai Chi by comparing the influence of Tai Chi practice on motor function and respiratory function between FC patients and HS using the lower-extremity muscle strength test, functional balance tests, and vital capacity test; (2) investigate the specific effects of Tai Chi from three aspects, including gastrointestinal symptom, autonomic nervous activity, and emotional state; and (3) explore the potential central responses of Tai Chi's specific and nonspecific effects by functional magnetic resonance imaging (fMRI).

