#### 2.3.1. Inclusion Criteria

Patients will be included in the study if they (1) reach the Rome IV Diagnostic Criteria for FC [14], (2) are right-handers and the age range is between 18 and 35, (3) have less than three CSBMs every week, (4) the Cleveland Constipation Score (CCS) score >10, and (5) provide a written informed consent form.

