#### 2.4.1. Inclusion Criteria

Subjects will be included if they (1) are right-handers and aged 18–35 years, (2) have no abnormalities during the physical examinations, (3) have passed the National Student Physical Health Standard test, and (4) provide written informed consent.

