## 3. Discussion

As a popular physical–mind exercise, Tai Chi is widely used in the prevention, treatment, and rehabilitation of various diseases. On the basis of the characteristics and related studies on Tai Chi, we put forward the original hypothesis that Tai Chi practice can produce relative specific effects and nonspecific effects on the human body.

The main purposes of this study include two aspects. First, this study tries to explore the physiological and psychological existence of the specific and nonspecific effects of Tai Chi by comparing the differences in the motor function, respiratory function, gastrointestinal symptoms, psychological manifestations, and HRV between FC patients and HS after Tai Chi practice. Second, this study tries to explore the potential central mechanism of the specific and nonspecific effects of Tai Chi practice by analyzing the potential cerebral activity changes induced by Tai Chi and their correlation with clinical variables. The study will provide a new approach for investigating the mind-body exercise, and the results might deepen our knowledge about Tai Chi.

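### Section 2.10.1 does not say that the FC–HS tests compare change from baseline; read as post-intervention tests, they mix the eligibility-driven baseline gap with any difference in effect

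*Protocol article*

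**What the plan says.** All references are to the Protocol article.

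- **Aim (section 1).** The nonspecific effects are to be studied by "comparing the influence of Tai Chi practice on motor function and respiratory function between FC patients and HS". Both groups receive the same 10 weeks of Tai Chi, so comparing its influence means comparing changes.
- **Tests (section 2.10.1).** Between groups: "The clinical data in the two groups (FC group and HS group) will be compared with two-sample *t*-tests". Within groups: "the comparisons of the baseline and after intervention in each group will be compared with a paired sample *t*-test". A Mann–Whitney test replaces the t-test for non-normal data. No change score, baseline adjustment or group-by-time term appears here or elsewhere in the article.
- **Timing (section 3, Discussion).** The first purpose is described as "comparing the differences in the motor function, respiratory function, gastrointestinal symptoms, psychological manifestations, and HRV between FC patients and HS after Tai Chi practice". Section 2.10.2 places the between-group fMRI comparison after the 10 weeks as well.
- **Eligibility.** FC patients need fewer than three complete spontaneous bowel movements (CSBMs) a week and "the Cleveland Constipation Score (CCS) score >10" (section 2.3.1). For HS, those with "gastrointestinal symptoms and signs are also excluded" (section 2.4.2). HS alone must "have passed the National Student Physical Health Standard test" (section 2.4.1).

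**The concern.** The trial's central conclusion is whether an effect of Tai Chi is disease-oriented (specific) or shared by patients and healthy people (nonspecific). That requires comparing the change in FC with the change in HS.

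The groups are not randomised against each other, and eligibility separates them before anyone practises. The gap is certain on constipation measures. It is possible on motor and respiratory outcomes, because only HS must pass a fitness standard. A comparison of values after practice therefore contains the starting gap as well as any difference in effect, and it can mislead in both directions: the gap can look like a differential effect, or a real differential effect can close the gap and vanish from the test.

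The paired tests do not fill the hole. A significant result in one group and a non-significant result in the other does not show that the two changes differ.

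**Working it through.** **Inputs from the article.** 36 per group before the drop-out allowance (section 2.2; 36/(1 − 0.10) = 40, which reproduces the recruitment figure); threshold p < 0.05 (section 2.10.1), taken as two-sided because sidedness is not stated. The 36 comes from a one-sample noninferiority question in FC, so the article has no sample-size figure for the FC–HS contrast to reproduce.

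**Assumptions.** The article gives no SDs, baseline gaps or correlations for these outcomes. Assumed: normal data, SD 1 at each visit, correlation 0.5 between baseline and week 10. The SD of change is then √(1 + 1 − 2 × 0.5) = 1, so SD of a visit and SD of change coincide. The simulations use 20,000 runs.

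**Step 1: what each test estimates.** Let B be the baseline difference HS − FC, and let C_FC and C_HS be the mean changes.
- Post-only difference: B + C_HS − C_FC.
- Difference in change: C_HS − C_FC.

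The post-only test answers the question only if B = 0.

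**Step 2: simulated share of trials with p < 0.05.**

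| Truth | Post-only test | Paired: FC only significant | Test on change |
|---|---|---|---|
| Both change 0.4 SD, gap 1 SD | 98.8% | 23% | 5.1% |
| Both change 0.4 SD, gap 0.5 SD | 55% | 23% | 4.8% |
| Both change 0.4 SD, no gap | 5.2% | 22% | 5.1% |
| FC improves 1 SD and closes a 1 SD gap, HS unchanged | 5.1% | 95% | 98.9% |

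In the first three rows the effect is truly the same in both groups, so any rate above 5% is a false signal of difference.

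**Step 3: paired tests under equal change, by formula.** With paired-test power p in each independent group, P(FC significant, HS not) = p(1 − p).
- Change 0.33 SD: p = 0.486; 0.486 × 0.514 = 0.25.
- Change 0.4 SD: p = 0.646; 0.646 × 0.354 = 0.23.
- Change 0.5 SD: p = 0.831; 0.831 × 0.169 = 0.14.

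**Step 4: what a test on change can deliver at 36 per group.**
- 95% CI half-width: t(0.975; 70) × √(2/36) = 1.994 × 0.2357 = 0.47 SD of change.
- 80% power needs a difference of about 0.67 SD of change. At a true difference of 0.4 SD the power is 0.39.
- If the true difference is zero, the 95% CI lies wholly inside ±0.5 SD in about 12% of trials, inside ±0.6 SD in about 42% and inside ±0.7 SD in about 67% (simulation, normal data).

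**The case against.** **The post-only reading is not stated in the analysis section.** This stands. Section 2.10.1 gives neither the time point nor whether raw or change values are used. The Discussion sentence is not an analysis specification, and the explicit wording in section 2.10.2 concerns fMRI. A two-sample t-test on change would fit both section 2.10.1 and the aim. So a reader might infer that the plan rules out a test of change, and the text does not support that. It does support this much: the test is left open, the nearest descriptions point to post-intervention values, and the wording needs correcting on either reading.

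**No decision rule is written down.** This also stands. The article nowhere says that significance in FC but not in HS means a specific effect, or that a non-significant FC–HS test means a nonspecific one. Sections 2.7.2 and 2.7.3 sort outcomes into the two classes beforehand. But that sorting is the hypothesis under study, and the tests named are the only ones offered for checking it.

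**Some tempting figures overstate the harm.**
- Exactly one paired test is significant in 2p(1 − p) = 50% to 28% of trials for equal changes of 0.33 to 0.5 SD. Half of those are HS-only results, which nobody would read as disease-oriented. The relevant share is 25% to 14%.
- Missing a true 0.4 SD difference in change 61% of the time (1 − 0.39) is a property of a test on change at 36 per group. It limits the remedy too and is not a harm of the present wording.
- A reader might infer that the week-5 data go unused. Section 2.10.1 does not exclude them from the two-sample tests.

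**Model details belong in an analysis plan.** Agreed. A mixed model, covariates or an equivalence margin are choices an article may leave out. Which quantity is compared between the groups is different: the article names its tests, and as worded they do not secure its stated aim.

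**Conclusion.** The point holds in this form: section 2.10.1 does not tie the FC–HS comparison to change from baseline, the surrounding text points to post-intervention values, and the only other tests are within-group. Followed that way, the analysis can give a wrong answer in either direction.

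The size depends on the unknown baseline gap. With identical change in both groups, the post-only test is significant in about 99% of trials for a 1 SD gap and 55% for 0.5 SD, and is at its nominal level with no gap. With a 1 SD gap that FC closes completely, the post-only test detects the effect in about 5% of trials, against about 99% for a test on change. FC-only significance on paired tests under equal change runs at about 25% to 14% whether or not there is a gap. These figures rest on the assumed SDs, correlation and gaps.

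The one-sample question in FC, on which section 2.2 bases the sample size, is untouched.

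**What to change.** In section 2.10.1:

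1. State that the FC–HS comparison is the difference in change from baseline to week 10, reported with its 95% CI, for motor, respiratory, psychological and HRV outcomes. Use a two-sample test on change, or a group-by-time contrast that includes week 5 where it was measured. HRV is recorded only at baseline and the end (section 2.7.3 and Table 1), so it needs the two-time-point version.
2. Keep the paired tests as descriptions of change within each group, not as the basis for saying that the groups differ.
3. State that a non-significant difference in change is not evidence of a shared effect, and that the CI will be used to show which differences remain compatible with the data.
4. For CCS, PAC-SYM and PAC-QOL, base the conclusion on change within FC. HS without gastrointestinal symptoms start near the floor of these scales and have little room to improve.

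**Cost.** Wording only: baseline and week-10 measurements are already scheduled in both groups. The price is candour about precision. With a half-width of about 0.47 SD and 80% power only from about 0.67 SD, many outcomes may stay unclassified. The change contrast also does not remove regression to the mean in FC patients selected on symptom cut-offs, which should be stated as a limitation.
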